### Randomization

3.3

Trial participants will be randomly assigned to one of the two arms in an equal ratio using a web-based randomization system. Randomization will be performed by the Singapore Clinical Research Institute (SCRI) on a pay-for-service arrangement. The randomization sequence will be concealed from the investigators, ensuring allocation concealment.

#### Standardization

3.3.1

Participants randomized to the mushroom powder intervention arm will be instructed to consume daily for 24 months. Electronic diary apps will be used to monitor compliance. The Pleurotus citrinopileatus extract will be supplied by Guangdong Yuewei Edible Fungi Technology Co., Ltd. (Guangzhou, China). Dried fruiting bodies (1 kg) were mixed with distilled water (25 L), then boiled under reflux for 2 h. The slurry was filtered and centrifuged (4,000 rpm, 15 min) to yield the extract, which was vacuum-concentrated to 1/10 volume, blended with 20% maltodextrin, and spray-dried at high temperature. Final powder contained 1.0% ergothioneine (HPLC-UV quantification). We selected a daily ergothioneine dose of 10 mg (two 500 mg capsules of Pleurotus citrinopileatus extract at 1% ET), corresponding to 70 mg ET per week. This falls within the range of prior human interventional studies: Yau et al. administered 25 mg ergothioneine per capsule, three times per week (75 mg ET/week) for one year (Yau et al., 2024); Mori et al. gave four 250 mg tablets of Hericium erinaceus dry powder (96% purity, ~960 mg powder per dose) three times daily (~2.88 g powder/day) for 16 weeks—both regimens were well tolerated (Mori et al., 2009). Participants in the control arm will consume placebo capsules. Participants and assessors will be blinded to the randomization. The mushroom powder will be derived from the mushroom species *Pleurotus citrinopileatus*. The dried fruiting bodies of *Pleurotus citrinopileatus* have an ergothioneine content of 10.0 mg/g (dry weight). The following figure is a diagram of the *Pleurotus citrinopileatus* body and its preparation method (Figure 2).

**Figure 2 fig2:**
[figure not shown]
The diagram of the *Pleurotus citrinopileatus* body and its preparation method.

### Assessments and outcomes

3.4

Participants will undergo questionnaire-based interviews, cognitive testing, and clinical assessment. The primary endpoint is 24-month MMSE change; secondary endpoints include SDMT, CTT, RAVLT, CDR, plasma ergothioneine, inflammatory markers, NfL, and epigenetic age.

We will administer the Singapore–Chinese version of the MMSE to eliminate bias from items incongruent with Singapore’s geography and culture (e.g., seasons, state/province), thereby enhancing the accuracy and sensitivity of cognitive assessment in our local Chinese population(Feng et al., 2012), in which: (1) the seasons question is replaced by “Without looking at your watch, what time is it?”; (2) the city/town question is replaced by “What area are we in?”; (3) the state/province question is replaced by “Which part of Singapore is this place (North, South, East, West or Central)?”; (4) the three-item immediate and delayed recall words are adapted to “ball, flag, tree” (English) or “柠檬, 锁匙, 气球” (Chinese); and (5) the sentence repetition item is adapted to “no ifs, ands or buts” (English) or “四十四只石狮子” (Chinese). Trained study psychologists will administer RAVLT, Color Trails Test 1&2, and both written and oral versions of the SDMT to evaluate memory, executive function and information processing speed, respectively. The above neuropsychological tests have been used in local research studies by the Principal Investigator and colleagues (Feng et al., 2006; Feng et al., 2009; Lee et al., 2012). CDR (Morris, 1993) will be administered to assess dementia severity (CDR global score). Only participants with a CDR global score of zero will be recruited. Depressive symptoms will be measured using the 15-item Geriatric Depression Scale (GDS-15)(Sheikh and Yesavage, 1986) for older participants and Patient Health Questionnaire (PHQ-9) for middle-aged participants (Kroenke et al., 2001). The PHQ-9 is a short questionnaire that measures depression severity based on the DSM-5 criteria (Kroenke et al., 2001). The GDS has been used in local studies by the principal investigator and coworkers (Feng et al., 2012; Ng et al., 2009) Dietary intake will be assessed using a Food Frequency Questionnaire (FFQ)(Whitton et al., 2017) that the trial participants will complete at baseline and follow-up visits. Information on supplements that may have neuroprotective effects, such as curcumin/turmeric, *Gingko biloba*, and polyunsaturated fatty acids, will also be collected using a questionnaire that will be designed by trial dietitian. Venous blood specimens will be collected both for the measurement of biological markers and for liver and renal panel tests for safety monitoring. To ensure consistency and minimize the influence of other factors, biological sample will be collected in the morning between 8.15 to 9.30 a.m. following an overnight fast, both at baseline and 24 months post-baseline. Table 1 provides a summary of measurements and study visits schedule.

**Table 1 tab1:** Measurements and visit schedules.

S.no.	Measurement	Baseline	1 year	2 years
1	Socio-demographics	√		√
2	Lifestyles, dietary intake (FFQ)	√	√	√
3	Medical conditions, medications, supplements	√	√	√
4	Mini mental state examination (MMSE)	√	√	√
5	GDS-15 or PHQ-9 for depressive symptoms	√	√	√
6	Neuropsychological tests (3 cognitive tests as a battery)	√	√	√
7	Clinical dementia rating (CDR)	√	√	√
8	Handgrip strength, repeated chair rise test, blood pressure	√	√	√
9	Venous blood sample collection and blood-based biomarkers	√		√

For cognitive measures, we selected locally validated and normed tools to ensure sensitivity to changes over time. We have carefully considered and included a panel of biological markers based on potential pathways. We will measure pro-inflammatory cytokines (such as hs-CRP, TNFα, IL-1, IL-6, etc.), and neurofilament light chain (NfL) as a non-specific biomarker of neurodegeneration (AD). We will also measure the genetic polymorphism of *APOE* gene and the DNA methylation profile. This biological approach has a clear advantage over traditional trials that only assess clinical outcomes and clinical laboratory tests.

The level of inflammatory biomarkers and NfL in the blood will be assessed using an ELISA assays as previously described(Cheah et al., 2017). We decided to measure pro-inflammatory cytokines because both inflammatory damage has been well documented in both AD pathophysiology and the biology of aging(Querfurth and LaFerla, 2010) and the biology of aging(Franceschi et al., 2018). NfL levels have been suggested as a blood-based biomarker for neurological diseases (Fan et al., 2023). The level in plasma increases in preclinical Alzheimer’s disease (AD) before symptoms appear (Preische et al., 2019) and correlate with MCI and other AD hallmarks, such as brain shrinkage and tau tangles observed on PET scans (Raket et al., 2020). Here, we will use plasma NfL as a systemic biomarker for cognitive decline. We will generate epigenome-wide methylation data using the state-of-the-art Illumina Infinium MethylationEPIC BeadChip (Pidsley et al., 2016) on the HiScan system. The array covers over 850,000 methylation sites per sample at single-CpG site resolution, and provides unparalleled coverage of CpG islands, RefSeq genes, ENCODE open chromatin, ENCODE transcription factor binding sites, and FANTOM5 enhancers, as well as regions identified by the ENCODE project as potential enhancers. This epigenome approach will help shed light on unknown pathways and is superior to traditional approaches that focus on a limited number of genes. We will calculate epigenetic clocks using established methods and use these clocks as a quantitative measure of biological age compared with chronological age.

Furthermore, we will measure plasma ergothioneine levels using liquid chromatography-mass spectrometry at baseline, 12 months and 24 months. Correlating changes in blood ergothioneine levels with cognitive outcomes and with pathological and aging-related biological markers will shed light on ergothioneine’s mediating role in the hypothesized relationship between mushroom consumption and cognitive aging. The inclusion of biomarkers of both a mushroom-derived compound and of aging and dementia represents a novel approach not previously adopted in human studies.

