**Measurements:**

Cognitive function including Mini Mental State Examination, Rey Auditory Verbal Learning Test, Symbol Digit Modality test, Clinical Dementia Rating etc. along with mental health and biological markers will be measured at baseline, 1 year, and 2 years after baseline.

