To examine the underlying protective mechanisms: The levels of biomarkers will be treated as continuous variables. Changes in biomarkers will be calculated by comparing post-intervention levels to pre-intervention levels from intervention and control and represented in percentage (%). These changes will then be compared between the intervention and control groups. Furthermore, paired two-tailed t-tests will be performed to assess whether biomarker levels differ between pre-intervention and post-intervention measurements within each group (control and intervention). To analyze the ergothioneine data, we will use a “change-versus-change’ approach, using repeated ergothioneine measurements as predictors to examine their relationship with changes in cognition and other biomarkers. We will further employ Structural Equation Modeling (SEM) to assess how the intervention affects cognitive function, with ergothioneine as a hypothesized mediating factor. In the SEM, we will adjust for age, sex, education (social class proxy), BMI, APOE ε4 status, baseline supplement use (curcumin, Ginkgo, omega-3), individual metabolic variations by including plasma liver enzymes (ALT, AST) and baseline renal function & ergothioneine levels as covariates, and compliance rate. Interaction terms will test effect modification.

To examine the epigenetic changes associated with ET-Rich mushroom consumption: Analysis of epigenome-wide methylation data will be performed using a modified version of the CPACOR pipeline(Lehne et al., 2015). Briefly, we will normalize marker intensities by quantile normalization. Single-marker tests using logistic regression will be used to examine the association of mushroom consumption with each autosomal CpG site (yes/no), adjusted for age and sex. Principal components from intensity values of Infinium control probes will also be included as covariates in the regression models. Finally, the association results will be adjusted for the genomic control inflation factor. We will subsequently develop a methylation risk score (MRS) model by taking a weighted approach (by effect size) for the CpG loci identified to be associated with mushroom consumption. Figure 3 describes the flow of study participants.

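### The blood schedule contradicts itself at 12 months: Table 1 omits a draw that plasma ergothioneine needs, and so leaves the liver and renal panels no scheduled draw during dosing

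*Protocol article*

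**What the plan says.** All of this is in the protocol article.

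- **Purpose of the blood (section 3.4).** "Venous blood specimens will be collected both for the measurement of biological markers and for liver and renal panel tests for safety monitoring".
- **Timing in the text (section 3.4, next sentence).** Fasting morning samples are taken "both at baseline and 24 months post-baseline".
- **Timing in Table 1.** Row 9, "Venous blood sample collection and blood-based biomarkers", is ticked at baseline and 2 years. Its 1-year cell is empty. No other row concerns blood, and the liver and renal panels have no row of their own.
- **Plasma ergothioneine (end of section 3.4).** It is measured "using liquid chromatography-mass spectrometry at baseline, 12 months and 24 months".
- **Abstract, Measurements.** Cognitive function "along with mental health and biological markers will be measured at baseline, 1 year, and 2 years after baseline".
- **Use of the values.** Section 3.4 lists plasma ergothioneine as a secondary endpoint. Section 3.5 uses its repeated values as predictors in a change-versus-change analysis and treats ergothioneine as the mediator in a structural equation model. Liver and renal measures appear there only as covariates: "plasma liver enzymes (ALT, AST) and baseline renal function".
- **Dosing (section 3.3.1).** Participants in the intervention arm "will be instructed to consume daily for 24 months".

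**The concern.** Two places in the article schedule no blood at 12 months and two require it. Staff usually work from the visit table, so the likely practical result of leaving the conflict in place is that no tube is drawn at the 1-year visit.

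Two things depend on that tube. The first is the middle ergothioneine measurement. A missed sample cannot be recovered later, and the mechanistic analyses would have only the two end points. The second is the liver and renal panel. The article gives it a monitoring purpose but no timing of its own, so its timing has to be read from the general blood schedule. Under Table 1 the first result after baseline would arrive when dosing ends, too late to guide care while the product is being taken.

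**Working it through.** **Step 1. Set the schedules side by side.**

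| Place | What is scheduled | Baseline | 12 months | 24 months |
|---|---|---|---|---|
| Section 3.4, sampling sentence | Biological sample | yes | no | yes |
| Table 1, row 9 | Venous blood and blood biomarkers | yes | empty | yes |
| Section 3.4, ergothioneine paragraph | Plasma ergothioneine | yes | yes | yes |
| Abstract, Measurements | Biological markers | yes | yes | yes |
| Section 3.5, model covariates | Liver enzymes, renal function | renal only | not stated | not stated |

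Plasma cannot be measured without a blood draw, so the third row requires one that the first two rows leave out. The empty cell in Table 1 is not an artefact of text extraction, because it agrees with the sampling sentence.

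**Step 2. Count draws during dosing.** Dosing runs from month 0 to month 24.

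- Sampling at {0, 24}: 0 draws strictly inside the period; longest gap 24 − 0 = 24 months.
- Sampling at {0, 12, 24}: 1 draw inside the period; longest gap 12 − 0 = 24 − 12 = 12 months.

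**Step 3. Effect on the ergothioneine data.** Each participant who completes the trial gives 2 values under Table 1 and 3 under the ergothioneine paragraph. Changes between successive visits number 2 − 1 = 1 and 3 − 1 = 2. Table 1 does schedule cognitive testing at 1 year. Under its blood row, the cognitive change from 0 to 12 months would have no matching ergothioneine change.

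**Step 4. Effect on the panels.** Their time points must come from the shared blood schedule:

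- Table 1: no draw during dosing on which a panel could be run.
- Ergothioneine paragraph: one such draw. The purpose sentence in section 3.4 could be read to cover it, but nothing says that the panel is run on that sample.

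**Step 5. Size of the repair.** Inputs are 600 participants (section 3.2) and 20% attrition at 24 months (section 3.5). The article does not say when the attrition occurs, so a range is given for the 12-month visit:

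- All attrition before month 12: 600 × 0.80 = 480 panels.
- No attrition before month 12: 600 × 1.00 = 600 panels.

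**Step 6. The plan's own figure.** The article's one computed design figure is the sample size. With d = 0.30, two-sided α = 0.05 and 90% power, the t-test solution is 234.46, which rounds up to the stated 235 per arm. Then 235 / 0.80 = 293.75, or 294, against 300 planned. It reproduces and has no bearing on this point.

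**The case against.** The strongest reply concerns the safety panels. No statement gives them a time. The sampling sentence is about clock time and fasting, and may be meant only to standardise the before-and-after biomarker comparison. Table 1 is introduced as a summary. A condensed article commonly leaves the timing and review of safety laboratory tests to the full protocol, which is not shown. How often to run a panel on an edible-mushroom extract is also a matter of judgement. Finally, the 1-year visit is not empty of clinical review: medical conditions, medications, supplements and blood pressure are all recorded.

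Most of this stands, and it limits the claim. A reader might infer that the trial has no laboratory safety check during dosing. The documents do not support that, because the article itself implies a 12-month draw that the panels could share. A reader might also infer an unmonitored liver or kidney hazard. The article reports no such signal and gives no event rate. Section 3.3.1 does say of the two earlier regimens it cites that "both regimens were well tolerated". They lasted 16 weeks and one year and used other products, but the article draws no 24-month safety claim from them.

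The reply does not reach the contradiction itself. That does not rest on silence: the article states two schedules, and they disagree about whether blood is drawn at 12 months.

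**Conclusion.** The point holds as a scheduling contradiction with two consequences. If Table 1 is followed, the 12-month ergothioneine value is not collected, and the liver and renal panels have 0 scheduled draws between the start and end of 24 months of daily dosing, against 1 if the 12-month draw is kept.

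The first consequence follows directly from the text. The second assumes that the panels follow the general blood schedule. That is the natural reading of section 3.4 and of a table row covering venous collection as a whole, but it remains an inference.

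The primary endpoint (24-month MMSE change), its analysis and the sample size are unaffected. The contradiction is worth correcting before the first 1-year visits, because a sample not taken then is lost.

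**What to change.** 1. Split row 9 of Table 1, or add a row, so that a 1-year venous draw is scheduled for plasma ergothioneine and for the liver and renal panel. State that the panel result is clinically reviewed when it is reported.
2. Leave cytokines, NfL and methylation at baseline and 24 months unless the sponsor intends otherwise. Simply ticking row 9 at 1 year would appear to schedule all of these as well, at far greater cost.
3. Amend the sampling sentence in section 3.4 to include the 12-month draw under the same fasting and time-of-day conditions. Amend the abstract to say which markers are measured at 1 year.

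The cost is a few lines of text and about 480 to 600 routine panels. No visit is added, and there is no draw beyond the one that the ergothioneine paragraph already requires.

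If the sponsor intends Table 1 to stand, the 12-month time point should be removed from the ergothioneine paragraph and the 1-year biomarkers from the abstract. The panel times should then be stated, and any laboratory safety statement limited to participants sampled at 24 months. That choice gives up the middle ergothioneine value.

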### Methods of analysis

3.5

To test the relationship between mushroom consumption and cognition among cohort participants: A linear regression model will be used to assess how baseline mushroom consumption predicts future cognitive changes. A log-binomial regression model will be used to compare the proportion of incidental cognitive impairment cases in the subgroups defined by mushroom consumption. A sensitivity analysis will be performed using a log-binomial model for repeated measures, including assessments at the 5-year follow-up and controlling for major demographic, medical, and lifestyle factors. Pre-specified subgroup analyses will stratify by baseline cognitive status (MMSE ≥ 27 vs. < 27), sex, and education level (≤ secondary vs. > secondary). Interaction terms will test for differential intervention effects.

*A priori* power calculation was performed using G*Power 3.1. Assuming a small-to-medium effect size of Cohen’s d = 0.30 in 24-month MMSE change, two-tailed *α* = 0.05 and 90% power, 235 subjects per arm are required. Allowing 20% attrition at 24 months (Jacobsen et al., 2021), we plan to enroll 300 per arm.

To test the effects of ET-Rich mushroom powder on cognitive function among RCT participants: A linear regression model will be performed to compare changes in cognitive scores at 24 months between the intervention and control arms. A sensitivity analysis will be performed using a general regression model for repeated measures, including assessments at 12 months and controlling for major demographic, medical and lifestyle factors at baseline.

To examine the underlying protective mechanisms: The levels of biomarkers will be treated as continuous variables. Changes in biomarkers will be calculated by comparing post-intervention levels to pre-intervention levels from intervention and control and represented in percentage (%). These changes will then be compared between the intervention and control groups. Furthermore, paired two-tailed t-tests will be performed to assess whether biomarker levels differ between pre-intervention and post-intervention measurements within each group (control and intervention). To analyze the ergothioneine data, we will use a “change-versus-change’ approach, using repeated ergothioneine measurements as predictors to examine their relationship with changes in cognition and other biomarkers. We will further employ Structural Equation Modeling (SEM) to assess how the intervention affects cognitive function, with ergothioneine as a hypothesized mediating factor. In the SEM, we will adjust for age, sex, education (social class proxy), BMI, APOE ε4 status, baseline supplement use (curcumin, Ginkgo, omega-3), individual metabolic variations by including plasma liver enzymes (ALT, AST) and baseline renal function & ergothioneine levels as covariates, and compliance rate. Interaction terms will test effect modification.

To examine the epigenetic changes associated with ET-Rich mushroom consumption: Analysis of epigenome-wide methylation data will be performed using a modified version of the CPACOR pipeline(Lehne et al., 2015). Briefly, we will normalize marker intensities by quantile normalization. Single-marker tests using logistic regression will be used to examine the association of mushroom consumption with each autosomal CpG site (yes/no), adjusted for age and sex. Principal components from intensity values of Infinium control probes will also be included as covariates in the regression models. Finally, the association results will be adjusted for the genomic control inflation factor. We will subsequently develop a methylation risk score (MRS) model by taking a weighted approach (by effect size) for the CpG loci identified to be associated with mushroom consumption. Figure 3 describes the flow of study participants.

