## Discussion

4

Mushroom consumption is safe and is likely to be embraced by older adults in the community as a preventive intervention. Although compliance to the intervention may raise as a potential problem given the long study period of two years, we have proposed the following methods to address this potential difficulty and limitation: (1) study staff to give weekly phone calls to remind study participants of the regime they are supposed to follow; (2) compliance will be monitored via a simplified one-touch electronic diary app (large icons, single-button “check-in”), augmented by automated push/SMS/phone reminders, caregiver assistance for entry, and cross-validation using electronic pill caps. Compliance rate can be used as a covariate in statistical analysis. Per-protocol analysis will be conducted on a subsample of subjects who have a compliance rate of 85% or above. Although we include a placebo control and blinding, repeated cognitive testing may introduce practice effects. We will account for this by including the assessment session (visit number) as a covariate in our longitudinal models, and where validated alternate forms exist, we will use them. With positive results and strong evidence, mushroom consumption and supplementation could be recommended as an important and simple method for promoting cognitive health in aging individuals and as a public health measure at the population level. This will potentially lead to healthcare cost savings. Furthermore, this study could provide evidence for the development of new nutraceutical products, with further translational research. The proposed study will provide more definitive data on the efficacy of mushrooms in preventing cognitive decline among individuals who are at high risk of dementia. Translating these findings into clinical and public health practice could lead to improved cognitive health and a reduced incidence of dementia. This, in turn, could result in substantial savings on the direct and indirect cost of dementia care in Singapore. The research will also provide insights into the biological mechanisms underlying the putative effect of mushroom powder on cognitive decline. By addressing scientific questions not previously rigorously examined, this research can strengthen our conclusions regarding clinical efficacy.

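### The main RCT analysis regresses 24-month change on arm and leaves the 12-month scores and covariates to a sensitivity analysis; it is valid, but forgoes precision and some protection against dropout

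*Protocol article*

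**What the plan says.** The endpoint is fixed in the Assessments and outcomes section: "The primary endpoint is 24-month MMSE change". Table 1 schedules the MMSE and the neuropsychological battery at baseline, 1 year and 2 years.

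The Methods of analysis section then gives two models for the trial. The main one is: "A linear regression model will be performed to compare changes in cognitive scores at 24 months between the intervention and control arms". No covariate is named in that sentence. The other follows at once: "A sensitivity analysis will be performed using a general regression model for repeated measures, including assessments at 12 months", with adjustment described as "controlling for major demographic, medical and lifestyle factors at baseline". Baseline MMSE is not listed as a covariate in either model.

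The sample size rests on the same change score: "Assuming a small-to-medium effect size of Cohen’s d = 0.30 in 24-month MMSE change", with "two-tailed *α* = 0.05 and 90% power, 235 subjects per arm are required". Enrolment is set at 300 per arm, "Allowing 20% attrition at 24 months".

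**The concern.** The ranking of the two models is stated in the article, so it is a choice already made and not a detail left for later. Two things follow from it.

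First, a change score subtracts the whole baseline score, whereas regression on the baseline subtracts only the part that predicts follow-up. When the correlation between the two is below 1, the change score carries noise that adjustment would remove. The baseline score is collected on everyone, so adjusting for it costs nothing.

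Second, a 24-month change needs a 24-month score. Someone seen at 12 months who then leaves has no value for the main model unless one is imputed. With a fifth of participants expected to be lost by 24 months, part of the collected outcome data stays out of the headline test. The comparison then relies on a stronger assumption about dropout than a model that conditions on the 12-month score.

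At stake are the precision of the main estimate, its robustness to dropout, and which result is reported first if the two models disagree.

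**Working it through.** **Inputs from the article:** d = 0.30 on the 24-month change; two-sided alpha 0.05; power 90%; 235 per arm evaluable; 20% attrition; 300 per arm enrolled. **Assumed, because the article does not give them:** the correlation rho between baseline and 24-month MMSE, equal SDs at those two visits, and the dropout mechanism.

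**1. The plan's own figure.** Normal approximation: n = 2(1.960 + 1.282)²/0.30² = 233.5, so 234 per arm. The exact two-sample t-test gives 235 (power 90.07%), so the stated figure reproduces. For attrition, 235/0.8 = 293.75, so 294, which the plan rounds up to 300. Then 300 × 0.8 = 240 per arm with a 24-month score, for which the t-test power is 90.7%.

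**2. Precision.** Let both visits have SD s.
- Variance of the change score: 2s²(1 − rho).
- Residual variance after adjusting for baseline: s²(1 − rho²).
- Ratio: (1 − rho²)/[2(1 − rho)] = (1 + rho)/2.

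The same raw effect then has standardised size 0.30/√ratio, and the required n is 233.5 × ratio, rounded up.

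| Assumed rho | Variance ratio | Variance saved | n per arm for 90% (change score: 234) | Power at 240 per arm (change score: 90.7%) |
|---|---|---|---|---|
| 0.5 | 0.75 | 25% | 176 | 96.6% |
| 0.6 | 0.80 | 20% | 187 | 95.6% |
| 0.7 | 0.85 | 15% | 199 | 94.5% |
| 0.8 | 0.90 | 10% | 211 | 93.3% |
| 0.9 | 0.95 | 5% | 222 | 92.0% |

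The gain keeps its sign throughout and shrinks towards zero as rho approaches 1.

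**3. Dropout.** This was simulated with no true effect, 20% dropout in each arm, and three assumed sets of correlations (baseline–12 months, baseline–24 months, 12–24 months): 0.6/0.5/0.6, 0.7/0.6/0.7 and 0.8/0.7/0.8. Bias is in SDs of the 24-month change, for a comparison of those with a 24-month score.

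| Assumed dependence of dropout on 12-month change | Bias, change-score comparison | Bias, using baseline and 12-month scores |
|---|---|---|
| None | about 0 | about 0 |
| Same in both arms (log-odds 0.5 per SD) | about 0 | about 0 |
| One arm only, log-odds 0.5 per SD | 0.054 to 0.058 | about 0 |
| One arm only, log-odds 1.0 per SD | 0.097 to 0.105 | about 0 |

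Dropout that depended on the level of the 12-month score in one arm only, and not on the change, gave no bias for the change score under the first correlation set. There the 12-month score is equally correlated with both other visits. A difference between arms is therefore necessary for bias under no effect, but not always sufficient. Milder mechanisms that differ by arm gave about 0.04.

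To turn a bias b into type I error with 240 per arm: SE = √(2/240) = 0.0913, and the rejection rate is 1 − Φ(1.96 − b/SE) + Φ(−1.96 − b/SE). This gives 7% at b = 0.04, 9% at 0.05 and 19.5% at 0.10. A bias of 0.10 is a third of the design effect of 0.30.

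**The case against.** The strongest reply is that the plan is coherent. Endpoint, sample size and main model all use the 24-month change, and the 235 per arm reproduces. In a randomised comparison without differential informative dropout, a change-score analysis is unbiased and holds its type I error, and chance baseline imbalance is already in its standard error. The repeated-measures model is planned too. All of this stands. What it leaves is a valid analysis ranked above a more precise one.

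A reader might go further in four ways that the article does not support:

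- **That the plan declares an unadjusted completers' analysis.** The article uses neither term. The lack of covariates in the main model is inferred from the contrast with the sensitivity sentence. The analysis set and the handling of missing scores may be in a full protocol or analysis plan not shown, and their absence here is no fault.
- **That the result will be biased by dropout.** Nothing in the article suggests that the mechanism differs by arm. Controls also take capsules, and participants and assessors are blinded. The repeated-measures approach does well in the simulation partly by construction, because dropout there depends on scores that it uses.
- **That the main model contradicts the practice-effect promise in the Discussion.** That promise concerns "including the assessment session (visit number) as a covariate in our longitudinal models". The repeated-measures model can carry that term, and a single-visit change regression is not such a model. There is no conflict.
- **That the two planned models need only trade places.** As described, the sensitivity model does not name baseline MMSE, so promoting it unchanged would not clearly deliver the precision gain.

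**Conclusion.** The point holds as a worthwhile improvement and not as an error in planning. The article fixes a single-visit change regression as the main analysis and places the 12-month data and the covariates in a sensitivity analysis, with baseline MMSE a named covariate in neither.

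The certain part is lost efficiency: 25% to 5% of the variance for rho between 0.5 and 0.9, given equal SDs, in a trial that still has about 90% power at its assumed effect. The conditional part is exposure to dropout. It applies only if missing scores are not imputed and dropout tracks the 12-month course differently by arm. Under the mechanisms assumed here it amounts to about 0.04 to 0.10 SD and a type I error of roughly 7% to 20%; with the same mechanism in both arms there is none. Those dropout figures show what could happen and do not forecast what will. It would be wrong to conclude that the trial is underpowered or that its type I error is inflated as planned.

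**What to change.** Make a repeated-measures model of the 12- and 24-month MMSE scores the primary analysis:

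- Include all randomised participants with any post-baseline score, analysed as randomised.
- Fit arm, visit, arm-by-visit, baseline score and baseline-by-visit, with an unstructured covariance.
- Take the arm difference at 24 months as the primary contrast. With the baseline score in the model, this is also the adjusted difference in 24-month change, so the endpoint does not alter.
- Keep the 24-month change regression as a sensitivity analysis.
- Use the same model for SDMT, CTT and RAVLT.

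The cost is a fresh specification of the repeated-measures model, chiefly adding the baseline score, written before unblinding. No new visits, data or participants are needed, and the sample size can stay as it is.
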